# MyBack - effectiveness and implementation of a behavior change informed exercise programme to prevent low back pain recurrences: a hybrid effectiveness-implementation randomized controlled study protocol

**DOI:** 10.1186/s12891-024-07542-7

**Published:** 2024-06-05

**Keywords:** Low back pain, Recurrences, Exercise, Behaviour change, Hybrid type I implementation/ effectiveness, Primary health care

## Abstract

**Background:**

Low back pain (LBP) is a common health condition and the leading cause of years lived with disability worldwide. Most LBP episodes have a favourable prognosis, but recurrences within a year are common. Despite the individual and societal impact related to LBP recurrences, there is limited evidence on effective strategies for secondary prevention of LBP and successful implementation of intervention programmes in a real-world context. The aim of this study is to analyse the effectiveness of a tailored exercise and behavioural change programme (MyBack programme) in the secondary prevention of LBP; and evaluate acceptability, feasibility and determinants of implementation by the different stakeholders, as well as the implementation strategy of the MyBack programme in real context.

**Methods:**

This protocol describes a hybrid type I, randomized controlled trial to evaluate the effectiveness and implementation of MyBack programme in the context of primary health care. The Behaviour Change Wheel framework and FITT-VP principles will inform the development of the behaviour change and exercise component of MyBack programme, respectively. Patients who have recently recovered from an episode of non-specific LBP will be randomly assigned to MyBack and usual care group or usual care group. The primary outcome will be the risk of LBP recurrence. The secondary outcomes will include disability, pain intensity, musculoskeletal health, and health-related quality of life. Participants will be followed monthly for 1 year. Costs data related to health care use and the MyBack programme will be also collected. Implementation outcomes will be assessed in parallel with the effectiveness study using qualitative methods (focus groups with participants and health providers) and quantitative data (study enrolment and participation data; participants adherence).

**Discussion:**

To our knowledge, this is the first study assessing the effectiveness and implementation of a tailored exercise and behaviour change programme for prevention of LBP recurrences. Despite challenges related to hybrid design, it is expected that data on the effectiveness, cost-effectiveness, and implementation of the MyBack programme may contribute to improve health care in patients at risk of LBP recurrences, contributing to direct and indirect costs reduction for patients and the health system.

**Trial registration number:**

NCT05841732.

## Background

Low back pain (LBP) is the most prevalent musculoskeletal health condition worldwide, affecting about 568 million people of all social classes and age groups [1]. According to Global Burden of Disease study 2019, LBP remains the leading cause of years lived with disability (YLDs), accounting for 63.7 million YLDs (an increase of 47% since 1990) [1, 2]. In Portugal, the estimated point prevalence of LBP was 26.4% [3] and recent national projections suggest an increase of more than 8% by 2050 [4]. LBP has been consistently associated with long-term disability, anxiety and depressive symptoms, and high costs associated with loss of working hours and early retirement [3, 5]. LBP episodes are one of the main reasons for consultation in primary health care [6, 7]. The levels of disability due LBP are responsible for most of the healthcare costs associated with treatment, including high medicalization rates, imaging tests, re-consultation, and physiotherapy, among others [3, 5].

LBP is potentially a long-term health condition characterized by a variable clinical course and multiple interrelated symptomatic episodes [8]. Most LBP episodes have a favourable prognosis, with 90% of patients recovering within 6 weeks [8, 9]. However, LBP recurrences are very common, with 1-year recurrence rates ranging from 33 to 70% [10, 11], of which 40% of people seek health care [11]. Recurrences are the main reason for the consumption of health resources due to LBP [11, 12], as well as for sickness certificates and daily activities limitations. In addition, repeated episodes of recurrence seem to have an increasing duration, work impact and costs, further contributing to the burden of this health condition [5, 13].

By contrast with thousands of studies that assess treatment effects, robust evidence about secondary prevention of LBP remains scarce [14, 15]. Furthermore, studies that analyse specific treatments targeting the symptoms of a current episode of LBP have shown no effects on recurrence rates [14]. A systematic review on this topic suggested that post-discharge exercise programmes seem to be the best strategy with promising results in reducing the risk of LBP recurrence [14]. Likewise, another systematic review with meta-analysis found that exercise alone or in combination with education could reduce 35% and 45% of the risk of an LBP episode, respectively [16]. Despite these results, the same systematic review pointed out that exercise programmes seem to be particularly effective in reducing LBP recurrences in the short to medium term (< 1 year), progressively losing their protective effect over time [16].

Two recent randomized clinical trials seem to corroborate these data, showing that education and exercise programmes can reduce care seeking compared to minimal intervention [17], although they do not meaningfully reduce the risk of LBP recurrence [17, 18]. In both studies, the authors reported low adherence to exercise programmes (consisting mostly of autonomous exercise), which may help to explain the limited effects of exercise on LBP recurrences over time [17, 18]. Considering this issue, it has been argued that exercise programmes should be designed to facilitate the regular and autonomous performance of exercise beyond the intervention period, namely be driven by a theory of behaviour change [14, 19–21]. The use of theory within interventions may provide a greater understanding of the determinants of the target behaviours (i.e., regular exercise) as well as help to identify effective techniques to modify them. Indeed, previous research has suggested that theory-driven interventions are more effective than those that are not, promoting adherence to intervention and maintenance of long-term self-management behaviours such as physical activity [22–24].

On the other hand, previous studies do not integrate comprehensive and long-term assessments of the impact of preventive interventions in real contexts of practice such as primary health care (including their cost-effectiveness) [25] or whether its implementation is possible with sufficient fidelity to preserve its effectiveness. The implementation of innovative practices in new contexts is a complex process that includes multiple potential barriers [26]. The integration of different stakeholders, such as patients, healthcare professionals, or healthcare managers in the implementation process, as well as understanding the context, are critical elements for increasing the potential success and future sustainability of innovative practices [27]. Furthermore, this shared and interactive process is essential to assess effectiveness in context and identify strategies that facilitate and accelerate the knowledge transferability and innovative practices to the clinical practice.

This study seeks to address these issues, describing a hybrid effectiveness-implementation study, which will (1) analyse the effectiveness of a tailored exercise and behavioural change programme and usual care versus usual care alone in the secondary prevention of LBP and (2) evaluate acceptability, feasibility, and determinants of implementation by the different stakeholders, as well as the implementation strategy of the MyBack programme in real context.

## Methods

This protocol is reported in accordance with the Standards for Reporting Implementation Studies (StaRI) checklist [28] and was previously register in Clinicaltrials.gov (NCT05841732). The study timeline is shown in Fig. 1.

**Fig. 1 Fig1:**
[figure not shown]
Study timeline

### Study design and setting

We will conduct a hybrid type I, pragmatic, randomized, controlled, and multicentre study to evaluate the effectiveness and implementation of an intervention programme in the context of primary health care (PHC). The study will be carried out over a period of 3 years in 10 primary health units (HU) located in both urban and rural areas, which provide healthcare (including physiotherapy services) to approximately 950 000 people. All PHCs/HUs partners in the MyBack study have recently implemented an interdisciplinary stratified model of treatment for patients with an episode of LBP [29]. Therefore, the MyBack study will be conducted alongside with the current model of treatment for patients who recovered from the LBP episode in the different partner HU. The MyBack trial design (#Aim I: Effectiveness) is illustrated in Fig. 2.

**Fig. 2 Fig2:**
[figure not shown]
Study design (#Aim I: Effectiveness)

### Participants

Eligibility criteria will be assessed by trained general practitioners in each partner HU. Participants will be eligible if they: (1) have recently recovered (within the last 3 months) from an episode of non-specific LBP (with or without leg pain and of any duration), defined as pain limited to the region between the lower margins of the 12th rib and the gluteal folds to which it is not possible to attribute a specific anatomical or nociceptive physiopathological cause [30, 31]; (2) are aged between 18 and 65 years; (3) are able to read and speak the Portuguese language; (4) have a mobile phone capable of receiving and sending text messages; (5) and do not have any medical contraindication to exercise. Recovery from an LBP episode is defined as having a pain score of “0” or “1” on a 11-point Numeric Pain Rating Scale (NPRS) for, at least, 30 consecutive days [32]. This means that only participants without pain (or minimal pain – 1/10 NPRS) for at least a month are eligible. Additionally, patients will be excluded if they have a diagnosis, or symptoms consistent with, severe depression or other psychiatric condition, if they are pregnant, if they have undergone back surgery in the prior 6 months, or if their proficiency in Portuguese language is inadequate to complete self-reported outcome measures.

### Recruitment

Potential participants will be recruited from 10 HUs through the collaboration of at least one physiotherapist (PT) from each HU. At the discharge session of the usual treatment programme for an LBP episode, potential participants will receive an information sheet giving details of the MyBack study and will be invited to participate by their PT. Patients who agree to participate will sign the informed consent form and will proceed to a standardized assessment to establish full eligibility. Patients who agree to participate in the study but who have not yet reached the recovery criteria at that time will be contacted every 15 days over a 3-month period, until they reach it. This contact will be made by text message according to the following statement: “On an 11-point scale where “0” means no pain and “10” the worst pain imaginable, in the last month, my back pain was always “0” or “1” (yes / No).

### Baseline assessment

After eligibility criteria have been confirmed, participants will attend a baseline assessment. All participants will complete the baseline assessment on-site that will include a questionnaire of prognostic factors for LBP recurrence and long-term disability [33–35] and specific instruments to assess pain intensity, functional disability, musculoskeletal health, and health-related quality of life (HRQoL). A description of the study measures is presented in Table 1.

**Table 1 Tab1:** Overview of study measurement

Construct/ Variables	Instrument/ Test	Time point			
		Baseline	Monthly	3, 6 & 12-months	
Demographics	Self-reported questionnaire [33–35]	x			
Clinical		x			
Work Situation**		x	x		
LBP recurrences	The return of LBP with a minimum duration of 24 h, with a pain intensity ≥ 2 on an 11-point numerical scale, preceded by a minimum period of 30 days without pain [32]		x		
Pain intensity**	Numeric Pain Rating Scale (0 to 10) [54, 65]	x	x	x	
Functional Disability**	Roland Morris Disability Scale (0 to 24) [56]	x	x	x	
Musculoskeletal Health (Subdomains: pain severity, physical function, work interference, social interference, sleep, fatigue, emotional health, physical activity, independence, understanding, confidence to self-manage and overall impact)	Musculoskeletal Health Questionnaire (0 to 56) [60, 66]	x		x	
Health-related Quality of Life	EuroQol, 5 dimensions, 5 levels (EQ-5D-5 L) questionnaire (0 to 1) [57]	x		x	
Aerobic capacity*	6-minute walking test [40]	x			
Trunk and lower limb resistance*	Trunk flexor test; Side bridge; Biering-Sörensen test; 60s sit to stand test [41–45]	x			
Trunk and lower limb flexibility*	Sit-and-reach test; Flexion and extension Schober test; Modified Thomas test [46–48]	x			
Motor Control*	Aberrant movement pattern and prone instability test [49, 50]	x			
Health care utilization and LBP Treatments (medical consultations, medication or imaging tests prescribed, referral to other interventions or to other medical specialties or services or sickness certificates) **	Self-reported questionnaire	x	x	x	

*MyBack group only; **Also measured when participants report a LBP recurrence in the screening that occurs every month.

### Randomization and blinding

A randomization scheme will be developed prior to the beginning of the trial, for each HU, by an independent statistician. The randomization will be performed using block randomization (randomly permuted block sizes 4 and 6) in a 1:1 ratio and stratified by HU. According to the randomization scheme, opaque envelopes, sealed and numbered consecutively, indicating the intervention that the participant will receive, will be prepared, and provided to the different local physiotherapists. Immediately after baseline assessment, the PT will open the sequence opaque envelope previously received from a centralized randomization service to allocate the patient to the MyBack (exercise, behaviour change and usual care) group or usual care group. Due to the nature of the study and interventions, it will not be possible to completely blind participants and physiotherapists. To minimise this limitation, it will be explained to participants that the study compares two different approaches for preventing LBP recurrences and participants allocated to usual care group will receive minimal educational intervention. Additionally, researchers responsible for outcome assessments and statistical analysis will remain blinded to group allocation.

### MyBack intervention programme and MyBack training programme

The Behaviour Change Wheel (BCW) Framework [36] will be used to guide the development of the behavioural component of the MyBack intervention programme and the training programme for physiotherapists involved in its implementation. Accordingly, the development process of both programmes followed the multi-staged approach described by Michie, Atkins, and West (2014) [37]: (1) defining the problem in behavioural terms; (2) selecting the target behaviour; (3) specifying the target behaviour; (4) identifying what needs to change; (5) identifying intervention functions; (6) identifying policy categories; (7) selecting behaviour change techniques; and, (8) determining the mode of delivery. These steps will be informed by an extensive literature review on the determinants of adherence to exercise and physical activity programmes, and effectiveness of behavioural change techniques. In addition, data from 4 focus groups will be used to inform the development of the two programmes: two focus groups will be conducted with patients who recently discharged from LBP treatment at the partner HUs in order to identify potential barriers and facilitators for adoption of regular exercise; two focus groups will be conducted with physiotherapists working in the partner HUs in order to identify potential barriers and facilitators for the implementation in real context of the MyBack programme. All determinants identified from the literature review and the focus groups will be analysed by two independent researchers through a deductive content analysis, based on the constructs of the COM-B model and Theoretical Domains Framework (as described in the BCW) [38]. A third researcher will be approached to settle disagreements.

In parallel, an inductive thematic analysis [39] of the focus groups’ data will be conducted to complement the deductive analysis. It is expected that this approach will allow a deeper understanding of the context and the needs of the participants not identified through the BCW codification. Moreover, potential feasibility and acceptability of the MyBack programmes will be also explored through the combination of both analyses.

Afterwards, the codification of the determinants will be linked to the intervention functions that best address them. Behaviour change techniques and modes of delivery that best tackle the intervention functions will be selected using the BCT taxonomy (BCTTv1) [37] and a mode of delivery ontology [38], respectively. This development process of MyBack programmes will be led by 5 members of the research team and each step will be revised by an external behavioural expert. The remaining team members will participate in consensus workshops on key decisions, applying the APEASE criteria (affordability, practicability, effectiveness and cost-effectiveness, acceptability, side-effects/ safety, and equity) to ensure that decisions are appropriate to the context. At the end, two mapping tables will be produced to inform the delivery of both MyBack programmes, comprising the BCTs and modes of delivery that might be used to target specific barriers related to the target behaviour. This process is illustrated in Fig. 3 and a detailed description of the content of both programmes will be published elsewhere.

**Fig. 3 Fig3:**
[figure not shown]
Flow diagram representing the development of the MyBack programmes based on the stages of the behaviour change wheel

### MyBack group

Patients in the MyBack group will participate in a patient-centred, tailored exercise programme informed by a behavioural change approach in addition to receiving usual care in their HU. The MyBack intervention programme will consist of 12 bi-weekly sessions (60 min each) over 6 weeks complemented by 12 exercise sessions to be carried out autonomously by the participants over the following 6 weeks (If the exercise programme includes an aerobic component, a third home-based exercise session will be included).

An initial clinical appointment will be scheduled to assess participants’ physical performance using specific tests, namely: aerobic capacity (6-minute walk test) [40], trunk (trunk flexor test, side bridge, Biering-Sörensen test) [41–44] and lower limb resistance (60s sit to stand test) [45], trunk and lower limb flexibility (sit-and-reach test, flexion and extension Schober test, Modified Thomas test) [46–48] and motor control (aberrant movement pattern and prone instability test) [49, 50]. Based on this assessment and on principles of exercise prescription (FITT-VP principles) [51], a tailored and structured exercise programme will be implemented. Therefore, the exercise component of the MyBack programme may include a variety of types of exercise including aerobic, strength, motor control or flexibility exercises. For example, if changes in motor control are not found, the participant will not perform motor control exercises, and emphasis will be placed on the other altered physical performance components.

All exercise sessions will be complemented with a behavioural change component aimed at promoting the adoption of the exercise programme (supervised and autonomous). This component aims to empower participants to integrate exercise and/or physical activity into their daily lives. Behavioural change component will be also tailored as physiotherapists will adjust content, delivery modes and behavioural change techniques to participant preferences and to individual determinants for target behaviour. Physiotherapists and participants will have access to documentation that will support the implementation of the MyBack exercise programme, including an online patient education package with key messages and BCTs (Physiotherapists) as well as videos supporting its exercise component (Physiotherapists and participants).

#### Usual care group

Participants allocated to the usual care group will be informed that they can access their GP in the usual way (GPs consultation, pain medication, referral for other treatments/ services) and that they should contact their GP if their condition worsens. In addition, they will receive a minimal educational intervention focused on symptom management and promotion of physical activity (“stay active”). This will be delivered in a 15-20-minute face-to-face appointment with their PT. They will be informed that they will be contacted periodically through a text message and by phone so their LBP condition can be monitored.

### Physiotherapist training programme

Intervention providers will be PTs working in the different partner HUs. Before the start of the study, all PTs will participate in online theoretical sessions (10 h) and in a three-day (24 h) practical workshop. The training programme will be focused on exercise testing and prescription in patients at risk of LBP recurrence and the development of necessary skills to promote the target behaviour. These include the use of BCTs targeting specific barriers to facilitate the adoption of regular exercise practice and the use of motivational interviewing principles to guide the whole intervention. As described above, PTs training programme will be developed using BCW framework to support PTs’ adoption of these new practices. It is expected the use of different modes of delivery, including role-playing activities, discussion of case scenarios and practical demonstrations.

Additionally, a clinical mentorship programme and evaluation of fidelity of the delivery will take place throughout the implementation. PTs will have ongoing support provided by two members of the research team, who will be available to discuss their clinical cases and clarify any doubts that may arise. Monthly, peer feedback and review of clinical cases will be provided to PTs by the MyBack team. PTs will also complete case report forms (CRF) detailing the interventions provided following the items of the Consensus on Exercise Reporting Template (CERT) checklist [52]. CRF will be reviewed regularly by two elements of research team to determine if the programme has been delivered as intended.

### Data collection and outcomes

#### #Aim I: effectiveness

Two trained researchers, blind to the patients’ group, will be responsible for the organization and data collection process. Every 30 days after the date of randomization, and over a 1-year period, the participants of both groups will receive a text message (SMS API (twilio.com)) with a yes/no question regarding LBP recurrence (In the last month did you have pain in your back, with an intensity equal or greater than 2, on a scale where “0” means no pain and “10” the worst pain imaginable and lasting at least 24 h?). This question is based on the definition of LBP recurrences: “the return of LBP with a minimum duration of 24 hours, with a pain intensity ≥ 2 on an 11-point numerical scale, preceded by a minimum period of 30 days without pain” [53]. All text messages will be sent and received through a specific SMS platform. In the presence of a LBP recurrence, the researchers will contact the participant by telephone to answer to a brief survey concerning the date of the recurrence and its impact (if the episode was severe enough to limit activity and/ or to cause care seeking), and to fulfil the self-reporting instruments (Table 1).

In the absence of a LBP recurrence, the researchers will contact the participants at three fixed data points: 3, 6 and 12 months after baseline, to fulfil the NPRS, Roland-Morris Disability Questionnaire (RMDQ), Musculoskeletal Health Questionnaire (MSK-HQ) and EuroQol (EQ-5D-3 L) (Table 1). The estimated patient’s burden to answer all the questionnaires is approximately 15 min. In addition, the participants’ medical records will be reviewed every 3 months. Data on any additional medical consultations, medication or imaging tests prescribed, referral to other interventions or to other medical specialities or services or sickness certificates will be recorded on the patient’s CRF.

Participants will remain on the trial unless they choose to withdraw consent, or they fail to answer three consecutive follow-up text messages. To prevent withdrawals and when a participant does not answer to 3 SMS text message or is not available at fixed follow-up time points, a maximum of three additional attempts will be made by telephone call.

The primary outcome of the study will be the risk of LBP recurrence, i.e. the percentage of participants experiencing one or more episodes of LBP recurrence within a 12-month follow-up period. Secondary outcomes include pain intensity, functional disability, musculoskeletal health and HRQoL. Pain intensity will be measured by a NPRS (11-point version). The NPRS has proven to be valid and reliable in patients with LBP [54, 55]. Disability status and HRQoL will be evaluated through the Portuguese versions of the Roland Morris Disability Questionnaire (RMDQ) and the EQ-5D, 5 L. Both self-reported measurement instruments have been cross-culturally validated to Portuguese language and showed good to excellent psychometric properties [56, 57]. The Portuguese version of the Arthritis Research UK Musculoskeletal Health Questionnaire (MSK-HQ) will be used to measured musculoskeletal health and 12 related subdomains (pain severity, physical function, work interference, social interference, sleep, fatigue, emotional health, physical activity, independence, understanding, confidence to self-manage and overall impact). The original and Portuguese version of MSK-HQ showed adequate psychometric properties in people with musculoskeletal pain [58–60].

Costs data will be collected to both groups from medical health records, and they will consist of all back pain-related recourse used within primary health care by each participant. For the MyBack group, the costs related to the MyBack programme (costs per session; costs of training physiotherapists; costs of materials and transport) will also be collected.

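### As printed, the monthly text behind the primary outcome asks about back pain without naming the low back, and no listed step checks location, so pain elsewhere in the back can be counted as an LBP recurrence

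*Protocol article*

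**What the plan says.** Under Participants, the protocol article defines the index condition as "pain limited to the region between the lower margins of the 12th rib and the gluteal folds". Under Data collection and outcomes (Aim I), it defines recurrence as "the return of LBP with a minimum duration of 24 hours, with a pain intensity ≥ 2 on an 11-point numerical scale", with a preceding pain-free period. The primary outcome is "the percentage of participants experiencing one or more episodes of LBP recurrence within a 12-month follow-up period".

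Events are found by a yes/no text sent every 30 days for a year. The printed question reads "In the last month did you have pain in your back, with an intensity equal or greater than 2", and goes on to explain the scale and require at least 24 hours' duration. A recurrence leads to a telephone call for "a brief survey concerning the date of the recurrence and its impact", plus the self-report instruments in Table 1. Separately, "medical records will be reviewed every 3 months", to record health care use.

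Under Usual care group, participants in that arm are told that they will be texted and phoned "so their LBP condition can be monitored".

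**The concern.** The printed question keeps two parts of the event definition, intensity and duration, but not the anatomical restriction. A participant with mid- or upper-back pain of 2 out of 10 lasting a day could truthfully answer yes. If nothing later asks where the pain was, that answer can enter the primary outcome as an LBP recurrence.

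Two things are at stake. First, the outcome would no longer measure quite what its name says. Second, non-lumbar events that arise about equally in both arms dilute the relative risk, in a trial with only 80% power for a large effect (a halving of risk). No analysis can remove these events afterwards if location was never recorded.

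**Working it through.** **Is there a location check anywhere in the article?**

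| Step | What is described | Location? |
|---|---|---|
| Monthly text | Back pain, intensity 2 or more, at least 24 h | Back only |
| Recurrence call | Date; impact (activity limitation, care seeking); questionnaires | Not listed |
| Table 1 | Instruments and time points | No location item |
| 3-monthly record review | Consultations, medication, imaging, referrals, sickness certificates | Not described as confirming events |

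An episode without care seeking may leave nothing in the medical record, so the record review could not fill the gap even if it were used for that purpose.

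**The plan's own figure.** Inputs from Sample size: 40% vs 20%, alpha 0.05, power 80%. Sidedness is not stated; two-sided is used here because it reproduces the result (one-sided would give 64). With pooled variance:

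n = [1.96 × √(2 × 0.30 × 0.70) + 0.842 × √(0.40 × 0.60 + 0.20 × 0.80)]² / 0.20² = 81.2, or 82 rounded up. The arcsine formula gives 80.3, or 81. The stated 81 per group is therefore reproduced and is not in question. Power at 81 per group is 79.9%.

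**Effect of unlocated events.** Let p be the true 12-month LBP recurrence risk. Let f be the chance that a participant with no LBP recurrence answers yes at least once because of other back pain. Then:

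observed risk = p + (1 − p) × f

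The article gives no value for f. The values below are assumptions, equal in both arms.

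| f | Usual care | MyBack | Relative risk | Difference | Power, 81 per group |
|---|---|---|---|---|---|
| 0% | 40.0% | 20.0% | 0.50 | 20 points | 79.9% |
| 2% | 0.40 + 0.60 × 0.02 = 41.2% | 0.20 + 0.80 × 0.02 = 21.6% | 0.52 | 19.6 points | 77% |
| 5% | 0.40 + 0.60 × 0.05 = 43.0% | 0.20 + 0.80 × 0.05 = 24.0% | 0.56 | 19 points | 73% |
| 10% | 0.40 + 0.60 × 0.10 = 46.0% | 0.20 + 0.80 × 0.10 = 28.0% | 0.61 | 18 points | 66% |
| 20% | 0.40 + 0.60 × 0.20 = 52.0% | 0.20 + 0.80 × 0.20 = 36.0% | 0.69 | 16 points | 54% |

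Power = Φ([d√n − 1.96√(2p̄(1 − p̄))] / √(p₁(1 − p₁) + p₂(1 − p₂))), where d is the difference and p̄ the mean of the two observed risks.

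**How far the direction depends on equal rates.** The observed relative risk exceeds 0.50 when 0.20 + 0.80 f(MyBack) > 0.5 × [0.40 + 0.60 f(usual care)], that is, when f(MyBack) > 0.375 × f(usual care). Suppose the programme also halved non-lumbar pain, with f in usual care between 5% and 20%. The relative risk would still be slightly diluted (0.51 to 0.54), but the difference would widen to 21–24 points and power would rise to 82–88%.

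**The case against.** The strongest reply is that the article is a condensed English account. Participants must read and speak Portuguese, and neither the message as sent nor the call script is shown. Either may name the low back. The text is introduced as a question about LBP recurrence, a footnote to Table 1 calls the monthly contact a screening, and trained researchers make the call. The setting also steers answers: patients are recruited at discharge from LBP treatment, and those in usual care are told that their LBP is being monitored. All of this stands. It lowers the likely number of misplaced events and makes checking the actual documents the first step. It does not remove the mismatch in what is printed, because the article gives the question in detail, lists what the call covers, and has location in neither.

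A reader might infer more than this, in four ways that the document does not support:

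- **That upper-back pain will be counted.** Nothing says that a yes for non-lumbar pain is scored as an event; the text only leaves that open.
- **That power will fall by a known amount.** The rate is assumed, and power could rise if the programme also reduced other back pain. The 40% control rate comes from a cited study and might already include some such events.
- **That the recovery text is flawed in the same way.** Its phrase, "in the last month, my back pain was always", goes to patients just treated for LBP and naturally refers to that episode. Eligibility is also assessed by trained general practitioners.
- **That exercise soreness in the MyBack arm biases against the programme.** The article offers no evidence for this, and a location item would not remove soreness felt in the low back.

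**Conclusion.** The point holds as a defect in the stated measurement of the primary outcome: the printed question is wider than the definition it is meant to apply, and no described step narrows it again. Pain outside the defined region can therefore be counted as an LBP recurrence.

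On the planned relative-risk scale, similar rates of such events in the two arms move the result towards no effect. The size is unknown. The move from 0.50 to 0.56 or 0.61, with power of about 73% or 66%, illustrates f = 5% or 10% in both arms and is not an estimate. It further assumes that the planned 40% and 20% are pure LBP risks. Very different reporting between the arms, which is possible because participants are not fully blinded, could change the direction.

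**What to change.** 1. Check the Portuguese message and the call script. If both already restrict the event to the low back, correct the wording in the article and stop there.
2. If they do not, word the monthly text as pain in the lower back, with a plain description of the region given under Participants (from the bottom of the ribs to the fold of the buttocks).
3. Make location an item of the existing recurrence call, and count an event only if the pain lies in that region.
4. If the trial is under way, add the call item now, report an analysis of located events alongside the main one, and state the date and nature of the wording change.

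The cost is a slightly longer text and one more item in a call that is already made. If introduced mid-trial, there is also a change of wording to report.
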